### Informed consent

Potential participants who meet all of the eligibility criteria will immediately be presented with the informed consent form to read and sign electronically. Individuals who click “decline to consent” will be locked out of the intervention and will be taken to the exit page. Individuals who do not respond will be taken to the exit page and subsequently will be contacted by research staff and asked if they would like to either “decline to consent” or “consent”. Individuals who click “consent” will be informed that they are enrolled as a participant in this study.

### Wave (W) 1 survey battery

Immediately after enrolling in this study, participants will be taken to a new page to complete the W1 survey battery. After completing the W1 survey battery, participants will be informed that a physical activity monitoring package (PAMP) will be sent to their mailing address within 1 week and then will be taken to the exit page. The specific content of both the W1 survey battery (e.g., demographics) and the PAMP will be detailed in the “Data collection” section of this manuscript.

### Sample size

Thirty participants will be targeted for enrollment in this study. There are three rationales for the target sample size. First, the target sample size fits well within the range of sample sizes often observed in pilot and feasibility trials [45]. Second, and with regard to aim 1 through aim 3 of this study, the target sample size is consistent with sample sizes observed in similar research [31, 46–48]. Third, and with regard to Aim 4 of this study, the target sample size is based on budgetary constraints and not a sample size determination for a desired level of statistical power [42–44]. Budgetary constraints preclude enrollment of more than 30 participants in this study.

### Randomization

Following completion of the W1 survey battery, participants will be randomly assigned to either the FFW group or the usual care (i.e., UC) group by the code programmed within the FFW website that is specified to achieve a 1:1 group (i.e., *n*_FFW_ = 15_,_
*n*_UC_ = 15) assignment.

Participants, center staff, and research staff will be blinded to participant group assignment.

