### Data collection

#### Study timeline

Three waves of data will be collected over a 13-week period (see Fig. 3), which is similar to both the 2015 FFW efficacy trial [36] and the 2018 FFW effectiveness trial [37]. Data collection at W1 will include the W1 survey battery and W1 physical activity monitoring. The W1 survey battery will be completed in week 1. The W1 physical activity monitoring will be completed in week 2. Participants will return physical activity monitoring items (to be detailed in the physical activity monitoring section) to the research staff in week 3. The intervention will be delivered in week 3 through week 6. Data collection at W2 will include the W2 survey battery and W2 physical activity monitoring. The W2 survey battery will be completed in week 7. The W2 physical activity monitoring will be completed in week 8. Participants will return physical activity monitoring items to the research staff in week 9. Data collection at W3 will include the W3 survey battery and W3 physical activity monitoring. The W3 survey battery will be completed in week 11. The W3 physical activity monitoring will be completed in week 12. Participants will return physical activity monitoring items to the research staff in week 13. The timeline for this study is similar to timelines used in other physical activity interventions in adults with obesity [6, 32, 33].

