Consistent with previous research [34], a brief cover letter, written and pictorial wear instructions, a daily log sheet regarding wear time, protocol checklist, and one preaddressed postage-paid, padded, return envelope (regular USA mail) will be included in the PAMP. In the cover letter, participants will also be directed to use their login credential to access electronic copies of the paper-based documents in the PAMP. Wear instructions will include the following: ensure that the belt is snug around the waist and that monitors are placed over the right hipbone crest at the anterior axillary line during wear time; begin to wear the monitors upon awakening the day after receipt for a seven-day interval; remove the monitors when sleeping or during water intensive activities (e.g., swimming, bathing) and reattach the monitors upon awakening or at cessation of water intensive activities; complete the daily log sheet online with date and time the monitors are put on and taken off each day; and return the monitors and belt on the day after a 7-day interval via the preaddressed postage-paid, padded, return envelope provided. On the day after a 7-day interval, participants will receive a reminder by e-mail and/or phone to return the belt and the monitors. At this time, participants will also be prompted to complete instruments designed to measure the acceptability of accelerometer-based assessment of physical activity and self-reported physical activity.

Upon return of the belt and the monitors the research team will follow a protocol based on previous research [34]. Data will be downloaded using a standard universal serial bus port. Belts will be laundered. Batteries in the monitors will be charged or changed if necessary. Monitors will be reinitialized for use. Within a few weeks of the return of the monitors, participants who provide usable data (to be described in the section on the ActiGraph wGT3X-BT) will be e-mailed (or mailed via regular mail if an e-mail address is unavailable) a preliminary estimate of their wear time and average minutes per day of MVPA in relation to broad categories of recommended MVPA per week (i.e., 0–4.21 min/day = minimal; 4.21–21.36 min/day = less than recommended; ≥ 21.36 min/day = meeting recommendation of 150 min/week). Participants who do not provide usable data will be informed that their average minutes per day of MVPA cannot be estimated due to insufficient data.

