##### Acceptability: qualitative

Themes that emerge from responses to the five qualitative items designed to assess acceptability will be analyzed at wave *W*, where *W* = W1 or W2 or W3. Possible improvements will be considered with regard to the protocol for accelerometer-based assessment of free-living physical activity within the FFW online intervention among adults with obesity in the USA. Specifically, improvements will be considered with regard to instructions for wearing the belt, acceptability of wearing of the belt, remembering to wear the belt, integration of wearing the belt into the daily routine, and why some participants may be unwilling to wear the belt as a part of new research study. The lower bound threshold is the presence of at least one potentially serious problem with the accelerometer-based protocol that is unable to be addressed in a future study. The upper bound threshold is the absence of a potentially serious problem with the accelerometer-based protocol that is unable to be addressed in a future study.

#### Aim 4

Inferential statistical models under both an intent to treat (ITT) approach and a complier average causal effect (CACE) approach will be used to provide a preliminary effect size estimate for each direct effect depicted in the conceptual model (see Fig. 2) for the FFW online intervention (e.g., FFW → Physical Activity) at wave W, where W = W2 or W3. Using both an ITT approach and a CACE approach is consistent with data analyses from the 2015 FFW efficacy trial [36, 38, 39] and with the data analysis plan for the 2018 FFW effectiveness trial [37]. Covariates, the outcome at W1, and group assignment will be specified as predictors in both approaches. Threshold values for the traffic light system for the specific indicators that will be used to evaluate aim 4 are based on commonly used heuristics for Cohen’s *d* [76].

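### On the text's order, participants are randomised before W1 physical activity is measured, so the activity baseline used in the Aim 4 models is post-allocation; Table 1 also disagrees with the text on allocation order and wave windows

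*Protocol article*

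**What the plan says.** All references are to the protocol article.

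- **Enrolment and survey.** Under Wave (W) 1 survey battery: "Immediately after enrolling in this study, participants will be taken to a new page to complete the W1 survey battery". Demographics, self-efficacy and well-being are in this battery. Accelerometer and IPAQ activity are not.
- **Allocation.** Under Randomization: "Following completion of the W1 survey battery, participants will be randomly assigned to either the FFW group or the usual care". No week is named, and W1 monitoring is not made a condition. The same section states that participants, center staff and research staff are blinded.
- **Timing of W1 activity.** Under Study timeline: "The W1 survey battery will be completed in week 1. The W1 physical activity monitoring will be completed in week 2". On monitor return: "Participants will return physical activity monitoring items (to be detailed in the physical activity monitoring section) to the research staff in week 3". FFW is delivered in weeks 3 to 6.
- **Timing of the IPAQ.** Under W1, W2, and W3 physical activity monitoring: "On the day after a 7-day interval, participants will receive a reminder by e-mail and/or phone to return the belt and the monitors". At that time participants are also "prompted to complete instruments designed to measure the acceptability of accelerometer-based assessment of physical activity and self-reported physical activity".
- **Use of the W1 value.** In the Aim 4 analysis text: "Covariates, the outcome at W1, and group assignment will be specified as predictors in both approaches".
- **Table 1.** Allocation is at time 0. Every W1 assessment, surveys and demographics included, is under Post-allocation. The W2 column is weeks 3–7 and the W3 column is weeks 7–13.
- **Timeline for W2.** "The W2 physical activity monitoring will be completed in week 8", with the survey in week 7 and return in week 9. W3 runs over weeks 11 to 13.

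**The concern.** Baseline adjustment is safe when the arm cannot have influenced the covariate. Measuring the covariate before allocation guarantees that. Measuring it afterwards leaves the guarantee to concealment. Here the affected covariate is the W1 value of average daily MVPA, the study's primary physical activity measure.

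Two things are at stake. First, if someone learns or guesses the arm before or during W1 wear and changes activity in response, adjusting for that W1 value distorts the estimated effect. Second, anyone who skips W1 monitoring, or wears the monitors too little, does so as a randomised participant. Missing W1 activity values could then depend on arm. If monitoring came first, they could not.

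Table 1 adds a plain contradiction. The text puts the W1 survey before allocation and the table puts it after. The table's W2 column also ends before W2 monitoring takes place.

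**Working it through.** The plan gives no figure to reproduce; the check is mainly one of order.

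**1. Text against Table 1**

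| Event | Text | Table 1 |
|---|---|---|
| W1 survey battery | Week 1, before allocation | W1 column (weeks 1–3), after allocation |
| Allocation | After the W1 survey, week not named | Time 0, before the W1 column |
| W1 accelerometry | Week 2 | After allocation |
| W1 IPAQ, acceptability | Day after 7-day wear, about start of week 3 | After allocation |
| FFW delivery | Weeks 3–6 | Marked in the W2 column (weeks 3–7) |
| W2 survey, wear, return | Weeks 7, 8, 9 | Weeks 3–7 |
| W3 survey, wear, return | Weeks 11, 12, 13 | Weeks 7–13 |

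Both sources place W1 accelerometry and IPAQ after allocation. They disagree on the W1 survey. W2 wear (week 8) and return (week 9) fall outside the table's W2 column and inside its W3 column.

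**2. Which outcomes are affected.** On the text's order, W1 self-efficacy, subjective well-being and well-being actions precede allocation. Only physical activity, by monitor or by IPAQ, does not.

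**3. When the order produces bias.** Let b be the within-arm slope of the later outcome on the W1 value, and d the between-arm difference in W1 activity caused by knowledge of the arm, in SD units. Subtracting b × d in the adjustment shifts the estimate by that amount.

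- If the arm is unknown during W1 measurement, d = 0 and the shift is b × 0 = 0.
- The documents give neither b nor d. Purely as an illustration, assume b = 0.6 to 0.7 and d = 0.1 to 0.2. The shift is then 0.6 × 0.1 = 0.06 to 0.7 × 0.2 = 0.14 SD. The Aim 4 green threshold is 0.20.
- For scale, take the same 0.6 and 0.7 as correlations, with 15 per arm. The standard error of the adjusted effect is √(2/15) × √(1 − r²): 0.365 × 0.800 = 0.29 for r = 0.6, and 0.365 × 0.714 = 0.26 for r = 0.7. The largest illustrative shift is about half a standard error (0.14 / 0.26 = 0.54).

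**4. Routes by which the arm could become known.** The FFW login opens both the intervention and the data-collection site; the usual care login opens data collection only. Total gift cards are up to $45 against $30, and the FFW payment at W2 is tied to completing challenges. The article does not say when either difference becomes visible. W1 payment is $10 in both arms. The W1 IPAQ is answered at about the time FFW access opens, although it asks about the previous week.

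**The case against.** The strongest reply is that order alone biases nothing. A covariate measured after allocation but before treatment, and untouched by the arm, is valid for adjustment. Blinding is stated for participants and both staff groups. After the W1 survey the participant is told only that the monitoring package will be mailed, with no arm announced. Wear is in week 2 and FFW starts in week 3. This stands, and it limits the point to a risk. It does not remove it, because logins and payments differ by arm and the article does not say when participants see this.

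It is also fair that allocation in week 1 is an inference. The Randomization section gives an earliest point and no week, and Fig. 3 could not be seen. Nothing available makes W1 monitoring a precondition, however, and Table 1 agrees that W1 activity follows allocation.

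Three stronger readings are tempting but not supported:

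- **That the effect is biased by 0.06–0.14 SD.** Both inputs are assumed, so this is an illustration only.
- **That early allocation causes unequal baseline loss.** If 9 of 30 fail W1 monitoring (30%, still green for participation), the arms differ by 3 or more with probability 1 − 2 × C(15,4) × C(15,5) / C(30,9) = 1 − 0.573 = 0.427. That is chance imbalance under fair randomisation, and later unstratified randomisation would leave it unchanged. The real issue is loss that depends on the arm.
- **That Table 1 would lead to W2 activity being measured during the intervention.** Research staff mail the monitors, the timeline fixes week 8, and the table marks FFW itself under W2, so its columns read as study periods.

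**Conclusion.** The point holds in a limited form. As written, the W1 physical activity predictor in the Aim 4 models is measured after allocation, while the survey-based W1 outcomes are not affected on the text's order. Bias requires early knowledge of the arm or arm-dependent completion of W1 monitoring. The document neither shows that these will occur nor allows their size to be computed. The conclusion assumes that allocation follows promptly on the week-1 survey, as the text and Table 1 both suggest.

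The change is still worth making. Nothing in the article needs the arm before FFW access opens, and stated blinding is weak protection when logins and payments differ by arm. The mismatch between Table 1 and the text is a definite error, independent of any bias argument, and is corrected by relabelling.

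**What to change.** - **Move the trigger.** Have the website randomise after the W1 monitoring week and the W1 IPAQ prompt, immediately before FFW access opens in week 3. Include everyone who completed the W1 survey and has not withdrawn, whether or not their W1 monitor data are usable.
- **Do not stratify on W1 usability.** Monitors come back by mail in week 3 and usability needs download and processing, so it may be unknown at the trigger.
- **Keep the number consented as the denominator** for the Aim 1 participation and retention rates.
- **Correct Table 1.** Place W1 assessments before allocation, W2 assessments in weeks 7–9 and W3 in weeks 11–13, and show FFW delivery (weeks 3–6) separately.

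The cost is one change in the website code and a revised table. Participants who withdraw before week 3 are not randomised, a small downside. An IPAQ answered late, after the prompt, could still follow allocation. Missing W1 monitor data would remain, but wear completed on schedule could no longer depend on the arm.

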### Study design

The study design is a prospective, double-blind, parallel group randomized pilot trial. Recruitment of participants is scheduled to begin on 29 April 2019 at a local bariatric services center, hereto forward referred to as the center, within a major healthcare organization in the Midwest of the USA. Eligibility verification and data collection will be conducted online. Three waves of data collection (i.e., at W1, W2, and W3) will be collected over a 13-week period. Figure 3 provides a flow chart for recruitment of participants throughout data collection. Instruments designed to measure demographic information, anthropometric characteristics, acceptability and feasibility of accelerometer-based assessment of physical activity, self-efficacy, and well-being will be included in the study.

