#### Usual care

Participants assigned to the UC group (i.e., UC participants) will proceed through the preoperative weight management program provided by the center. The login credential for each UC participant will, however, provide access to a secure website to complete data collection (i.e., a survey battery and physical activity monitoring) at W1, W2, and W3. UC participants will have the opportunity to receive up to $30 worth of Amazon electronic gift cards, which is similar to previous research [36, 37]. Specifically, UC participants will receive $10 for completing the W1 survey battery and W1 physical activity monitoring, $10 for completing the W2 survey battery and W2 physical activity monitoring, and $10 for completing the W3 survey battery and W3 physical activity monitoring. UC participants will be given 4 weeks of 24 h access to the FFW online intervention approximately 1 month after data collection for this study is closed.

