#### Fun For Wellness

Participants assigned to the FFW group (i.e., FFW participants) will proceed through the preoperative program provided by the center and will be given 4 weeks of 24 h access to the FFW online intervention during data collection for this study. The login credential for each FFW participant will provide access to both the FFW intervention and to a secure website to complete data collection at W1, W2, and W3. FFW participants will have the opportunity to receive a total of up to $45 worth of Amazon electronic gift cards, which is similar to previous research [36, 37]. Specifically, FFW participants will receive $10 for completing the W1 survey battery and W1 physical activity monitoring; $25 for completing the W2 survey battery, W2 physical activity monitoring, and at least 30 post-introductory BET I CAN challenges; and $10 for completing the W3 survey battery and W3 physical activity monitoring. The remuneration plan at W2 is linked to completing post-introductory BET I CAN challenges to encourage compliance with the FFW intervention as suggested in previous research [36, 37].

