#### Self-efficacy to comply

Participants will be asked to respond to the following item in the W1 survey battery: *How confident are you in your current ability to get yourself to complete at least 30 Fun For Wellness post-introductory challenges within the next four weeks? Thoughtfully completing 30 post-introductory Fun For Wellness challenges may take approximately 4 h.* A five category rating scale structure, where 0 = no confidence, 1 = low confidence, 2 = moderate confidence, 3 = high confidence and 4 = complete confidence, will be implemented for this item, and in all self-efficacy scales from this point forward, based on previous research on effective self-efficacy rating scale structures [64]. Asking participants at the onset of an intervention to make a projection about their compliance with the subsequent intervention is consistent with previous research on compliance [65].

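### Participant blinding cannot hold when only one arm is given the online programme, so Aim 4 self-report effects at W2 and W3 are unblinded

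*Protocol article*

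**What the plan says.** The design label appears in the Abstract (Method) and again under Study design: "The study design is a prospective, double-blind, parallel group randomized pilot trial". The Randomization section says who is blinded: "Participants, center staff, and research staff will be blinded to participant group assignment".

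The arms are described just after that. In the Fun For Wellness section, participants in that arm "will be given 4 weeks of 24 h access to the FFW online intervention during data collection for this study", and "The login credential for each FFW participant will provide access to both the FFW intervention and to a secure website to complete data collection". The Study timeline places delivery in weeks 3 to 6. In the Usual care section, the login serves to "provide access to a secure website to complete data collection (i.e., a survey battery and physical activity monitoring) at W1, W2, and W3". UC participants receive the programme only about one "month after data collection for this study is closed". Neither section describes a sham or attention-control website.

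The Self-efficacy to comply section gives an item in the W1 survey battery that begins: "How confident are you in your current ability to get yourself to complete at least 30 Fun For Wellness post-introductory challenges". The item sets a window of the next four weeks. Randomization follows completion of that battery.

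The W2 payment is $10 in the UC arm. In the FFW arm it is $25 and depends on at least 30 challenges, and the stated purpose of that link is to encourage compliance.

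**The concern.** Blinding participants requires that the two arms look alike to them, or that participants do not know there is a contrast. Neither condition is met here. One arm uses a named programme for four weeks and the other does not, and participants have been told of the programme before they are allocated.

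What is at stake is the reading of Aim 4. That aim estimates each direct effect at W2 and W3, after access has diverged, and grades it by traffic light with green at d ≥ 0.20. The text describing the conceptual model gives seven constructs. Six are measured only by questionnaire: four self-efficacy scales, subjective well-being and well-being actions. The seventh, physical activity, is measured by two devices and also by the IPAQ, which is self-report. People who know that they received a programme meant to raise confidence and well-being may answer differently without any change in behaviour. A reader told that the trial was double-blind would set this explanation aside, and the results are meant to inform a definitive trial.

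**Working it through.** **Step 1. What each arm sees, from the sections named above**

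| Time | FFW participant | UC participant |
|---|---|---|
| W1 survey, before randomization | Asked about completing at least 30 FFW challenges in the next four weeks | Same question |
| Weeks 3 to 6 | Login opens the programme and the data-collection site | Login opens the data-collection site only |
| W2 payment | $25, tied to at least 30 challenges | $10 |
| After data collection closes | – | Programme access, about 1 month later |

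An FFW participant who works through challenges knows that the programme is being received. A UC participant was told of the programme and its time window and then sees that it does not appear. The first is certain. The second is a strong inference.

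**Step 2. Payments**

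The stated totals reproduce:
- UC: 10 + 10 + 10 = $30.
- FFW: 10 + 25 + 10 = $45.

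The whole $15 difference arises at W2 (25 − 10). The FFW payment can act as an incentive only on participants who know its condition. The article does not say that UC participants learn the FFW amount, so payment is supporting evidence and access is decisive.

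**Step 3. Which estimates are exposed**

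- Exposed: the W2 and W3 between-arm estimates in Aim 4 for the six questionnaire constructs and for IPAQ activity.
- Not exposed: the W1 survey scales, which precede randomization.
- Unclear: the W1 IPAQ. It is completed after the week 2 monitoring and so after randomization. The article does not say when participants learn their group.
- Largely unaffected: Aims 1 to 3, which rest mostly on single-group rates, agreement between instruments and acceptability of the belt.

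**Step 4. Illustration of sensitivity**

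The article gives no size for reporting bias, so the shift b below is an assumption. Take 15 per arm, no true effect, an unadjusted standardized difference and a normal approximation:

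SE = √(2/15) = 0.365

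P(green) = P(d ≥ 0.20) = 1 − Φ((0.20 − b)/0.365)

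| Assumed shift b (SD) | P(green) with no true effect |
|---|---|
| 0 | 0.29 |
| 0.1 | 0.39 |
| 0.2 | 0.50 |
| 0.3 | 0.61 |
| 0.5 | 0.79 |

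The planned models adjust for the W1 outcome and covariates, so the actual SE will differ. The table shows direction and rough scale only.

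**The case against.** The strongest reply concerns staff. Allocation is made by code in the website, the gift cards are electronic, and no person is said to issue them or see the amounts. The waiting-room help described under Recruitment belongs to the enrolment visit, before randomization. Staff are also said to be available for questions throughout the study, but only if needed. A reader might infer from the $25 and $10 payments, or from this contact, that staff blinding also fails by design. The document does not show that. Staff blinding is at risk if staff see the arm-specific W2 payments or answer questions about the programme, and that is as far as the text goes.

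A second reply is that what participants are told about the two arms is not visible, so it is too absolute to say that every participant knows the arm. This stands in part for UC participants, where the W1 item supports an inference and not a proof. It does not help for FFW participants, because no wording can hide from them that they are using the programme.

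A third reply is that this is a 30-person feasibility study, that Aim 4 is stated not to be powered, and that even without bias a null effect would show green about 29% of the time. This limits the weight of the point. It does not make the label correct, and bias, unlike sampling error, would carry over into a larger trial built on the same design.

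**Conclusion.** The point holds for participants. The article asserts a blinding that its own arms cannot deliver, and its stated limitations do not mention this. The consequence is confined to Aim 4: the W2 and W3 between-arm estimates from the self-efficacy scales, subjective well-being, well-being actions and the IPAQ should be read as unblinded.

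A reader might go further and treat every self-reported result in the study as compromised. The documents do not support that, because the W1 survey battery precedes allocation and Aims 1 to 3 are largely unaffected.

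The contradiction rests on the text alone and needs no assumption about the size of bias. The 0.1 to 0.2 SD shift is only an illustration. Device-measured MVPA is protected from reporting bias, but knowledge of the arm could still change behaviour or wear. This should be corrected, mainly as a matter of labelling and of what Aim 4 can claim.

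**What to change.** 1. In the Abstract, Study design and Randomization sections, replace the double-blind label and the blinding sentence. State that participants are not blinded, and name which staff are and how (for example, those processing ActiGraph data). Say whether those staff can see W2 payments or field questions about the programme.
2. Rest the Aim 4 activity effect on ActiGraph MVPA, with the IPAQ as supportive. The article makes average daily MVPA the primary activity measure, but the ActiGraph, the Fitbit Zip and the IPAQ all yield it, and the Aim 4 section does not choose. The ActiGraph shows the wearer no activity display, whereas the Fitbit Zip shows steps.
3. Report the Aim 4 self-report effects as unblinded and add reporting bias to the limitations.

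The cost is wording, plus the registry entry if it carries the same label, and one choice of instrument for Aim 4. Keeping named staff blinded may need a small procedural statement. Sample size and participant procedures do not change. The downside is a less favourable design label.
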